**Table 12: Safety Management Plan for Local Toxicity Observed on Pelvic Exam, including Colposcopy**

| Finding                                                                                                                                                                                                                                                                                                                                 | Management                                                                                                                                                                                                                                                                                                                                                                                                                                                                                                                                                                                                                                                                                                                                                                                                                                                                                                                                                                                                                                                                                                                                                                                                                                                                                                                                                                                                                                                                                    |
|-----------------------------------------------------------------------------------------------------------------------------------------------------------------------------------------------------------------------------------------------------------------------------------------------------------------------------------------|-----------------------------------------------------------------------------------------------------------------------------------------------------------------------------------------------------------------------------------------------------------------------------------------------------------------------------------------------------------------------------------------------------------------------------------------------------------------------------------------------------------------------------------------------------------------------------------------------------------------------------------------------------------------------------------------------------------------------------------------------------------------------------------------------------------------------------------------------------------------------------------------------------------------------------------------------------------------------------------------------------------------------------------------------------------------------------------------------------------------------------------------------------------------------------------------------------------------------------------------------------------------------------------------------------------------------------------------------------------------------------------------------------------------------------------------------------------------------------------------------|
| Vaginal bleeding                                                                                                                                                                                                                                                                                                                        | 
The source of the bleeding should be evaluated. Bleeding from the cervical os should be evaluated per standard of care. If the bleeding is from a previous biopsy site or a deep epithelial disruption, hemostasis should be attempted via direct pressure. Silver nitrate or Monsel's solution may also be applied. If adequate hemostasis is not obtained with these measures, electrocautery or suturing may be used. Samples may be collected per investigator discretion.
 
Product use may continue at investigator discretion.
                                                                                                                                                                                                                                                                                                                                                                                                                                                                                                                                                                                                                                                                                                                                                                                                                                                                                                                                             |
| 
Epithelial findings:
 
 
Erythema, edema, petechiae, ecchymoses (epithelium intact by definition) – includes cervicitis
 
Peeling (superficial epithelial disruption, by definition)
 
Ulcers, abrasions, lacerations with superficial or deep epithelial disruption
 
 | 
If an infection is suspected (e.g., due to erythema, vesicles, concomitant discharge, etc.):
 
A wet prep with KOH and pH, NAAT for GC/CT, and other tests may be done as indicated.
 
 
If candidiasis is diagnosed at Visit 3, the participant may be treated and Visit 2 and 3 rescheduled.
 
If candidiasis is diagnosed at Visit 4, the participant may be treated and Visit 4 rescheduled on cycle day 7 of the next cycle.
 
If candidiasis is diagnosed at Visit 5-8, the participant may be treated and the visit will continue.
 
If trichomoniasis, BV, or herpes simplex is diagnosed at Visit 3-6, the participant should be treated and discontinued.
 
If trichomoniasis, BV, or herpes simplex is diagnosed at Visit 7-8, the participant should be treated and the visit will continue.
 
 
If the finding is bleeding (which makes it deep epithelial disruption by definition), it should be managed as described under "Vaginal bleeding," above.
 
For all findings: If the area is small (less than approximately 3mm at the widest point), samples may be collected or the visit may be rescheduled, per investigator discretion. If the finding is >3 mm, consideration should be given to stopping product use and seeing the participant in unscheduled visits until the finding is resolved or resolving.
 |
| Vaginal discharge                                                                                                                                                                                                                                                                                                                       | 
A wet prep with KOH and pH should be done, and NAAT for GC/CT should be strong considered. If an infection is diagnosed, it should be managed as described under "Epithelial findings" above.
                                                                                                                                                                                                                                                                                                                                                                                                                                                                                                                                                                                                                                                                                                                                                                                                                                                                                                                                                                                                                                                                                                                                                                                                                                                                                   |

### 12.2.3. Genital Assessments

Genital samples (fluid and tissue) will be taken to assess safety as detailed below. Sample analysis will be performed at a central lab.

**Table 13: Safety: Genital Assessments**

|                                                                                             | Visit 3 | Visit 4                   |                                      | Visit 5 | Visit 6 | Visit 7 | Visit 8 |
|---------------------------------------------------------------------------------------------|---------|---------------------------|--------------------------------------|---------|---------|---------|---------|
|                                                                                             |         | Pre-insertion
Baseline | Post-insertion
(at assigned time) |         |         |         |         |
| CVL: soluble markers of mucosal immunity                                                    |         | ✓                         |                                      |         |         | ✓       |         |
| Genital Tissue: histology /immune cell activation                                           | ✓       |                           |                                      |         |         | ✓       |         |
| Genital Tissue: markers of mucosal alteration/ epithelial integrity (EVMS only)             | ✓       |                           |                                      |         |         | ✓       |         |
| Swabs: Microflora                                                               |         | ✓                         |                                      |         |         | ✓       |         |
| Microbial growth on swabs obtained from returned IVRs and microbial levels in returned IVRs |         |                           |                                      |         |         | ✓       |         |

 Includes: Semi-quantitative culture; Quantitative PCR (Copan Swab); Nugent Score (Gram Stain)

#### 12.2.3.1. Hematology and Blood Chemistry

CBC, lipids (fasting) and serum chemistry will be measured at Visit 1 (the baseline analysis for the study) and at Visit 7 prior to IVR removal. Changes will be assessed for safety.

#### 12.2.3.2. Pregnancy Screen

Pregnancy tests are required at Visits 1, 2, 3, 4 and 7 on all participants. Note, however, participants must be protected from pregnancy as described in Section 8.1 in order to be eligible for study participation.

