**Table 4: Relationship of Study Visits to IVR Day and Cycle Day**

|           | Screening/
Enrollment | Pre-treatment Cycle |         | IVR in place         |         |                      |                      | After IVR removal |         |
|-----------|--------------------------|---------------------|---------|----------------------|---------|----------------------|----------------------|-------------------|---------|
| Visit #   | Visit 1                  | Visit 2             | Visit 3 | Visit 4  | Visit 5 | Visit 6  | Visit 7  | Visit 8           | Visit 9 |
| IVR Day   |                          | ~ -14               | ~ -10   | 1                    | 2       | ~8                   | ~16-18               | ~17-19            | ~19-21  |
| Cycle Day | Any day                  | 21                  | 24      | 7                    | 8       | ~14                  | ~22-24               | ~23-25            | ~25-27  |

 IVR insertion

 Visit 6 to occur as close as possible to day of ovulation, but no later than Day 17. Some procedures from Visit 6 may be repeated if ovulation occurs after Day 17.

 IVR removal. Visit 7 should occur 8-10 days after Visit 6 or repeat Visit 6

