### 8.1. Inclusion Criteria

Volunteers must meet all of the following criteria prior to genital sampling at Visit 3.

- Age 18-45 years, inclusive
- General good health (by volunteer history and per investigator discretion) without any clinically significant systemic disease (including, but not limited to significant liver disease/hepatitis, gastrointestinal disease, kidney disease, thyroid disease, osteoporosis or bone disease, and diabetes)
- Currently having regular menstrual cycles of 26-35 days by participant report
- History of Pap smears and follow-up consistent with standard medical practice as outlined in the study manual or willing to undergo a Pap smear
- Protected from pregnancy by one of the following:
  - Sterilization of either partner. *Note: Women protected from pregnancy by sterilization of either partner must abstain from vaginal intercourse from 48 hours prior to Visit 3 until the sixth day after the last study visit.*
  - Willing to abstain from vaginal intercourse from Visit 1 until the sixth day after the last study visit.
- Willing to abstain from any other vaginal activity and the use of vaginal product other than the study product including tampons, spermicides, lubricants, and douches starting 48 hours before Visit 3 until the sixth day after the last study visit
- Vaginal and cervical anatomy that, in the opinion of the investigator, lends itself to easy colposcopy and genital tract sample collection
- Negative urine pregnancy test
- $P4 \geq 3$  ng/ml

- Willing to give voluntary consent, sign an informed consent form and comply with study procedures as required by the protocol

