## 9.6. Visit 6: Ovulation Sample Collection

Visit 6 should occur as close as possible to the day of ovulation, based on the ovulation predictor kit, or as soon as possible afterward. If the ovulation predictor kit does not turn positive by Day 16 of the participant's menstrual cycle, Visit 6 will occur no later than day 17 of the participant's cycle.

- The guidebook, including reported AEs, CTs and the menses diary, will be reviewed.

- The study staff will ask the participant if she followed the instructions regarding vaginal products and vaginal activity. If she did not, she will be reminded of protocol requirements and the visit will continue.
- A directed physical exam, pregnancy test, dipstick urinalysis (and possibly microscopy/cultures) and/or wet mount/pH will be performed, if indicated. If a symptomatic yeast or UTI infection is diagnosed, the participant will be treated with the shortest treatment consistent with the site's standard of care and the visit will continue. If pregnancy, symptomatic trichomoniasis or BV is diagnosed, the participant will be treated, as necessary, and discontinued.
- Blood will be drawn for TFV PK and LNG/SHBG PK/PD.
- A pelvic exam will be performed and the following procedures will be completed in the order listed. Findings will be managed as outlined in [Table 12: Safety Management Plan for Local Toxicity](#).
  - The biopsy sites from previous sampling will be assessed. Subsequent procedures will be done at the investigator's discretion.
  - Collection of vaginal aspirate for TFV PK.
  - Preparation of vaginal swab for TFV PK.
  - Preparation of vaginal swab for LNG PK.
  - Naked eye/colposcopic examination.
  - Collection of cervical mucus for LNG PK and PD.
- Participants who did not have a positive ovulation predictor kit result prior to Visit 6 will be instructed to continue testing with the kit following Visit 6. The participant will be asked to contact the site as soon as possible if/when the kit turns positive.
  - If the ovulation predictor kit turns positive following Visit 6, some procedures from Visit 6 will be repeated. Repeat Visit 6 should be scheduled as soon as possible following the positive result. The participant will be instructed to continue testing until the morning of repeat Visit 6.
  - At repeat Visit 6, the following procedures will occur:
    - The guidebook, including reported AEs, concomitant therapies (CTs) and the menses diary, will be reviewed.

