## 9.7. Visit 7: IVR Removal and Sample Collection

Visit 7 should occur 8-10 days after Visit 6 (or repeat Visit 6) to allow for the maximum number of days of IVR use in this menstrual cycle while ensuring that participants are seen for final genital sampling before their next menses begins.

- The guidebook, including reported AEs, CTs and the menses diary, will be reviewed.
- The study staff will ask the participant if she followed the instructions regarding vaginal products and vaginal activity. If she did not, she will be reminded of protocol requirements and the visit will continue.
- The participant will complete an acceptability questionnaire.
- A urine specimen will be obtained for a urine pregnancy test.
- A directed physical exam, dipstick urinalysis (and possibly microscopy/cultures) and/or wet mount/pH will be performed, if indicated. If a symptomatic infection is diagnosed, study procedures will continue per investigator discretion and the participant will be treated after completion of the visit procedures.
- Blood will be drawn for TFV and TFV-DP PK, LNG/SHBG PK/PD, CBC, serum chemistry, fasting lipids, and P4.
- A pelvic exam will be performed and the following procedures will be completed in the order listed. Findings will be managed as outlined in [Table 12: Safety Management Plan for Local Toxicity](#).
  - The biopsy sites from previous sampling will be assessed. Subsequent procedures will be done at the investigator's discretion.
  - Collection of vaginal aspirate for TFV PK.
  - Preparation of vaginal swabs for TFV PK, TFV PD, to test for microflora, and semen biomarkers as outlined in the study manual.
  - Collection of CVL for safety and TFV PD.
  - Naked eye/colposcopic examination.
  - Collection of cervical mucus for LNG PK.
  - Transvaginal ultrasound to assess endometrial thickness.
  - The IVR will be removed.
  - Collection and processing of one endometrial biopsy (EVMS only) for LNG PD as outlined in the study manual.
  - Collection and processing of up to three biopsies (up to five at EVMS) for safety and TFV and TFV-DP PK, as outlined in the study manual.
  - Appropriate post-biopsy instructions will be discussed with the participant.
- Post-removal ring procedures will be immediately carried out as outlined in the study manual.
- The participant will be given applicable reminders as described in Visit 4.

- Visit 8 will be scheduled to allow for sample collection 24 hours after IVR removal.

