## 9.10. Follow-up Call/Contact

The site will contact the participant about one to two weeks after the completion of study visits. She will be asked about AEs experienced and medications taken since the last visit. The participant will then be exited from the study, unless she has symptoms that require follow-up.

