#### **13.1.3. Serious Adverse Event (SAE) or Serious Suspected Adverse Reaction**

An AE or suspected adverse reaction is considered “serious” if, in the view of either the investigator or the sponsor, it:

- Results in death;

- Is immediately life-threatening;
- Requires in-patient hospitalization or prolongation of existing hospitalization;
- Results in persistent or significant disability or incapacity;
- Results in a congenital abnormality or birth defect; or
- Is an important medical event that may jeopardize the patient or may require medical or surgical intervention to prevent one of the outcomes listed above.

All SAEs starting with Visit 3, before treatment, during treatment, or by the time of the follow-up call/contact one to two weeks after the last study visit, whether or not they are related to the study, must be recorded on forms provided by CONRAD.

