Colposcopic findings should be reported on colposcopic finding CRFs and should not be reported as AEs on AE CRFs. Colposcopic findings are defined as severe when they involve deep disruption of the epithelium. An area of the epithelium with bleeding should be considered deeply disrupted. Severe colposcopic findings possibly, probably, or definitely related to product use must be immediately reported to CONRAD within 24 hours of discovery. In addition, a completed colposcopic finding CRF must be faxed or emailed to CONRAD as soon as possible.

Should a pregnancy occur, it must be reported as soon as possible to CONRAD and recorded on CONRAD’s pregnancy CRF. The participant will be discontinued from the study and appropriate exit procedures will be followed (Section 8.3.3). Note that pregnancy in itself is not regarded as an AE unless there is a suspicion that an investigational product may have interfered with the effectiveness of a contraceptive medication. If the participant has been exposed to study product, the course of the

pregnancy should be followed until it has an outcome (spontaneous miscarriage, elective termination, normal birth or congenital abnormality). If a pregnancy is diagnosed, study product to which the participant has been assigned may be unblinded. If the participant seeks care outside the site, every effort should be made to obtain her consent for the site to receive a copy of her medical records related to the pregnancy, its outcome and the health of the neonate, if applicable.

Reports of congenital abnormalities/birth defects are SAEs. Spontaneous miscarriages should be reported and handled as AEs. Elective abortions without complications should not be reported as AEs.

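### After the Visit 7 test, which is timed before menses, no scheduled step asks about menses once it is due, so a conception in the ring cycle could be missed

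*Protocol*

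**What the plan says.** - **Tests.** Section 12.2.3.2: "Pregnancy tests are required at Visits 1, 2, 3, 4 and 7 on all participants". Table 3 and Section 9.4 put the Visit 4 test before insertion. Section 9.6 adds a conditional test at Visit 6: "A directed physical exam, pregnancy test, dipstick urinalysis (and possibly microscopy/cultures) and/or wet mount/pH will be performed, if indicated".
- **Timing of the last test.** Table 4, footnote 3: "Visit 7 should occur 8-10 days after Visit 6 or repeat Visit 6". Section 9.7 gives the reason as "ensuring that participants are seen for final genital sampling before their next menses begins".
- **After Visit 7.** Sections 9.8 and 9.9 review the menses diary at Visit 8 and, where assigned, Visit 9. The fresh pages then given out are for concomitant therapies and AEs. On the later contact, Section 9.10 says: "She will be asked about AEs experienced and medications taken since the last visit". The Table 3 row that covers menses has no tick under follow-up.
- **Early stoppers.** Section 8.3.3 provides for questions on medications, AEs and genital symptoms. It requires neither a pregnancy test nor a question on menses.
- **Pregnancy.** Section 13.3 requires any pregnancy to be reported to the sponsor and an exposed one to be followed to its outcome. It does not regard pregnancy in itself as an AE, apart from a suspected interference with a contraceptive medication. It treats miscarriages as AEs, and adds: "Reports of congenital abnormalities/birth defects are SAEs".
- **Recording window.** Section 13.1.3 has SAEs recorded before treatment, during treatment "or by the time of the follow-up call/contact one to two weeks after the last study visit". Sections 13.1 and 13.4 use the same end point.

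**The concern.** The ring is worn in a single cycle, so a conception under exposure belongs to that cycle. The first ordinary sign of it would be menses that does not come. The only required test after insertion is taken before that sign can appear, and no later step is set up to notice it. The exit contact asks about AEs, a category that by Section 13.3 does not formally include pregnancy.

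At stake is participant safety follow-up, not an endpoint or an analysis. A woman exposed to an investigational ring could leave the study recorded as not pregnant, and the reporting and follow-up in Section 13.3 would never be triggered. The protocol allows for some lapses in abstinence. After insertion, reported non-adherence leads to a reminder and the visit goes on (Sections 9.5 to 9.7), and Section 14.6 foresees immune markers measured in the presence of semen.

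**Working it through.** **Inputs from the protocol.** Visit 6 at about cycle day 14, and insertion on day 7 counted as IVR day 1 (Table 4). Visit 7 is 8-10 days after Visit 6. Visits 8 and 9 are 24 and 72 hours after Visit 7. The contact is 7-14 days after the last visit (Section 9.10). On cycle length, Section 8.1 says: "Currently having regular menstrual cycles of 26-35 days by participant report".

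**Assumptions, not in the protocol.** Visit 6 is on the day of ovulation. The luteal phase lasts L = 12 to 16 days, and the first day of menses is L + 1 days after ovulation.

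**Step 1: reproduce Table 4.** Visit 7 = 14 + 8 to 14 + 10 = day 22-24. IVR day = cycle day − 6 = 16-18. Visit 8 = day 23-25 and Visit 9 = day 25-27. All agree with the table.

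**Step 2: date the exit contact.**
- Last visit is Visit 8: 22 + 1 + 7 = day 30 to 24 + 1 + 14 = day 39.
- Last visit is Visit 9: 22 + 3 + 7 = day 32 to 24 + 3 + 14 = day 41.
- Counted from Visit 6: 8 + 1 + 7 = 16 to 10 + 3 + 14 = 27 days.

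**Step 3: compare with menses.** By reported cycle length, menses is due on day 27 (26-day cycle) to day 36 (35-day cycle), always after a Visit 7 on day 22-24. By luteal length there are 3 possible Visit 7 days × 2 last visits × 8 contact lags = 48 timing combinations:

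| L (days) | Menses due, days after Visit 6 | Visit 7 test | Exit contact | Due by Visit 7 | Due by last visit | Due by contact |
|---|---|---|---|---|---|---|
| 12 | 13 | 3-5 days before | 3-14 days after | 0% | 17% | 100% |
| 14 | 15 | 5-7 days before | 1-12 days after | 0% | 0% | 100% |
| 16 | 17 | 7-9 days before | 1 day before to 10 days after | 0% | 0% | 98% |

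The 17% is 1 of 6 (only 10 + 3 reaches day 13). The 98% is 47 of 48 (only 8 + 1 + 7 = 16 falls short of 17). These are shares of scheduling combinations, equally weighted, not probabilities for women. If menses is counted from L days after ovulation instead, every gap moves by one day: for L = 14 the test is 4-6 days before and the contact 2-13 days after.

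**Step 4: what can be said about detection.** Let s be the sensitivity of the Visit 7 test for such a conception and r the chance that the woman reports it unasked. The share missed is (1 − s)(1 − r). The protocol gives neither s nor r, so both are varied:

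| s | r = 0 | r = 0.5 |
|---|---|---|
| 0.10 | 90% | 45% |
| 0.25 | 75% | 37.5% |
| 0.50 | 50% | 25% |
| 0.75 | 25% | 12.5% |
| 0.90 | 10% | 5% |

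The range runs from 5% to 90%, so no single share can be claimed.

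**Step 5: set the windows side by side.** Section 13.3 follows an exposed pregnancy to its outcome and classes a miscarriage as an AE and a birth defect as an SAE. Sections 13.1, 13.1.3 and 13.4 describe recording up to the contact one to two weeks after the last visit. A birth comes months later, and neither set of sections refers to the other on this point.

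**The case against.** The strongest reply is that exposed pregnancies should hardly occur. About 50 completers wear the ring for some 16-18 days. All are sterilized, have a sterilized partner or are abstinent from Visit 1, and even the sterilization-protected abstain from 48 hours before Visit 3. Adherence is checked at every visit from Visit 2, intercourse is recorded in the guidebook, semen-biomarker swabs are taken at Visits 4 and 7, and a woman may be withdrawn for serious non-adherence. The guidebook and study manual, which are not at hand, may also tell women to report a late period. All of this stands and limits the practical weight. It does not supply a step in the protocol that looks for a conception once menses is due.

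Three stronger readings are tempting and are not supported.

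- A reader might infer that Visit 7 holds the only test after insertion. Visit 6 has one if indicated. It is meant to be close to ovulation and no later than day 17, so it could hardly reveal a conception in that cycle, but it exists.
- A reader might infer that most exposed pregnancies would go undetected. That needs both a low test sensitivity and little self-reporting, and the protocol gives neither figure.
- A reader might infer that Section 13.3 and the AE/SAE windows contradict each other. Section 13.3 is conditional on a pregnancy being known and does not promise detection. It can be read as the specific rule that extends a general window, which does not forbid later recording. What remains is a missing cross-reference.

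**Conclusion.** The point holds as a modest gap in safety follow-up. The last required pregnancy test is placed before menses by design, and no scheduled step afterwards asks about menses once it is due. The existing exit contact falls at the informative time but does not ask the informative question. A conception in the ring cycle could therefore be missed.

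The timing result rests on Visit 6 being at ovulation and on the assumed luteal phase of 12 to 16 days. That the test precedes menses does not rest on the assumption, since Section 9.7 states it as the aim. No number of missed pregnancies can be derived, because the protocol gives no lapse rate, test sensitivity or self-report rate; the expected number is small. No endpoint or analysis population is affected. The change is worth making because it costs almost nothing.

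**What to change.** - In Section 9.10 and the follow-up column of Table 3, add one recorded item: has menses started since ring removal (yes/no, date).
- Keep menses on the guidebook pages given at Visits 8 and 9.
- Ask the same of women who stop early (Section 8.3.3). Their last contact may come before menses is due, so the sponsor should say when the item is asked.
- The sponsor should reconcile 9.10 and 12.2.3.2 with 13.3, including what follows a negative answer. That is a clinical decision and is left to the sponsor.
- Cross-reference Sections 13.1, 13.1.3 and 13.4 to 13.3, so that the recording window for exposed pregnancies agrees with follow-up to outcome.

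The cost is one question at a contact already scheduled, one line on existing pages, and a cross-reference in three sections. The downside is an occasional extra contact with a woman whose menses is merely late.
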